### Study design and settings

2.1

This study will be a single-blinded, randomized controlled trial with 2 parallel groups. It will be conducted at North China University of Science and Technology-affiliated hospital. This protocol was written and based on Standard Protocol Items: Recommendations for Interventional Trials guidelines. If they agree, they will sign an informed consent form. Only those participants who read and agree to the protocol and who sign the informed consent form will take part of the study, following the schedule described in Figure 1.

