#### Evaluation of efficacy and prognosis

2.6.2

A trained neurologist who will be unaware of the patient's morbidity was evaluated by the National Institutes of Health Stroke Scale (NIHSS score) at the time of patient admission, 24 hours after treatment, and 7 days after treatment. After discharge, the patient's prognosis was evaluated by the modified RanKin scale (mRS). We defined mRS score 0 to 1 points as cured and 0 to 2 points as good prognosis. After 7 days of treatment, the NIHSS score is reduced by 4 points and it is considered that it will be judged as effective in the early stage, and the NIHSS score is increased by 4 points or death will be judged as invalid or worse (Table 1).

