### Statistical analysis

2.8

All data will be analyzed using statistical software SPSS 25.0 (SPSS Inc, Chicago, IL). Under the condition that the measurement data meet the normality and homogeneity of variance, the before and after data of the same group are compared using the paired *t* test. If the data in the group are not normal, the Wilcoxon signed rank sum test in the nonparametric test can be used. The measurement data meet the conditions of normality and homogeneity of variance, and the data of the same period between the 2 groups are compared using the independent *t* test method. If the 2 sets of data do not meet the normal distribution, the Mann-Whitney *U* test in the nonparametric test makes it easy to compare the average level of data with no statistical significance. The count data are expressed in terms of frequency (f) and composition ratio. The composition ratio or percentage is tested by *χ*^2^ test. If the theoretical frequency T < 5 but T ≥1 in the data, the *χ*^2^ test with continuity correction is used. If any theoretical number is 0, Fisher test is used. To evaluate the treatment effect, Wilcoxon signed rank sum test will be used. All tests used a 2-sided test, with *P* < .05 indicating that the difference will be statistically significant.

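### Section 2.8 names a within-group paired test, the Wilcoxon signed-rank test, for the treatment effect and does not tie its listed between-group tests to that effect

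*Protocol article*

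**What the plan says.** All of the following is in the protocol article.

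- **Section 2.8, within a group.** For normal data, "the before and after data of the same group are compared using the paired" t test. The fallback is: "If the data in the group are not normal, the Wilcoxon signed rank sum test in the nonparametric test can be used".
- **Section 2.8, between groups.** For normal data, "the data of the same period between the 2 groups are compared using the independent" t test. The fallback begins "If the 2 sets of data do not meet the normal distribution, the Mann-Whitney" and names the U test. Proportions go to chi-square, with a continuity correction or Fisher's test for small expected counts.
- **Section 2.8, treatment effect.** "To evaluate the treatment effect, Wilcoxon signed rank sum test will be used". No other sentence in the section attaches a test to the treatment effect.
- **Section 2.8, level.** "All tests used a 2-sided test, with" a significance threshold of .05.
- **Section 2.1, design.** "This study will be a single-blinded, randomized controlled trial with 2 parallel groups".
- **Section 2.6.2, outcomes.** NIHSS is scored "at the time of patient admission, 24 hours after treatment, and 7 days after treatment". The section also defines two mRS categories (0–1 and 0–2) and two categories based on a 4-point NIHSS change, with death placed in the worse one.

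**The concern.** In a parallel-group trial the treatment effect is a contrast between separate sets of patients. The test named for it needs paired observations, and the only pairing here is a patient's own NIHSS at two times. Used that way, it asks whether patients changed, not whether thrombolysed patients changed more than the others. Section 2.5.2 gives both wake-up stroke groups the same other treatment, so change common to both arms is exactly what a treatment comparison has to remove.

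An analyst who follows the sentence literally could report a significant treatment effect when the arms do not differ. An analyst who notices the mismatch has to choose between the named test and the between-group tests, possibly after seeing the data.

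**Working it through.** **1. The section against itself.**

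| Task in section 2.8 | Normal data | Otherwise |
|---|---|---|
| Before/after, one group | paired t | Wilcoxon signed rank |
| Two groups, same time | independent t | Mann-Whitney U |
| Proportions | chi-square | corrected chi-square or Fisher |
| Treatment effect | Wilcoxon signed rank | – |

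The last row repeats the name used in the first row. Mann-Whitney has a row of its own, so on the section's own usage the treatment effect receives the within-group test.

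**2. What the test can answer.** Let d be a patient's change in NIHSS from admission. Within an arm, the signed-rank null hypothesis is that d is symmetric about 0. The null hypothesis of no treatment effect is that d has the same distribution in both arms. If both arms improve by the same amount δ > 0, the second hypothesis is true and the first is false in both arms. A rejection is then correct about change and uninformative about treatment.

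**3. Illustration of size.** The article states no power, SD, recovery or sample size, so it has no figure to reproduce.

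- From section 2.8: two-sided level 0.05, hence a critical value of 1.96.
- Assumed: SD of change σ = 4 points; common recovery δ = 0 to 3 points; n = 20 to 100 per arm; no true difference between arms.

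For normal changes and δ > 0, the large-sample approximation for one arm is

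P(reject) ≈ Φ(√(3n/π) × δ/σ − 1.96).

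- n = 30, δ = 2: √(90/π) = 5.352; 5.352 × 0.5 = 2.676; 2.676 − 1.96 = 0.716; Φ = 0.76.
- n = 50, δ = 2: √(150/π) = 6.910; 6.910 × 0.5 = 3.455; 3.455 − 1.96 = 1.495; Φ = 0.93.

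Simulation with unrounded changes (2,000 replicates per cell) gives these signed-rank rejection rates within the treated arm:

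| Common recovery | n = 20 | n = 30 | n = 50 | n = 100 |
|---|---|---|---|---|
| 0 points | 0.040 | 0.044 | 0.044 | 0.046 |
| 1 point | 0.198 | 0.272 | 0.398 | 0.675 |
| 2 points | 0.526 | 0.728 | 0.928 | 0.999 |
| 3 points | 0.863 | 0.974 | 0.999 | 1.000 |

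A second simulation, with changes rounded to whole points (4,000 replicates), gives 0.75 at n = 30 and 0.92 at n = 50 for a 2-point recovery. This agrees with the table and, allowing for the approximation, with the formula.

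**4. The between-group test on the same data.** Mann-Whitney U on change rejects in 0.040 to 0.059 of trials across all 16 cells. The Monte Carlo standard error is √(0.05 × 0.95/2000) = 0.005, so this is the nominal 5% within simulation noise.

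**The case against.** The strongest reply is that the plan is not without a between-group analysis. Section 2.8 lists valid two-group tests for measurements and tests for proportions, and section 2.6.2 defines efficacy largely by mRS and responder categories, which would go to chi-square or Fisher. This stands. A reader might infer that the efficacy conclusion has no control for the natural course, or rests on the signed-rank result alone. The article does not support that: nothing in it makes before/after NIHSS the primary endpoint.

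A reader might also infer that significance in one arm and not in the other would be declared efficacy. Such a split occurred in 14% to 49% of simulated null trials across six assumed settings. But the article states no such decision rule, so that range is not a property of this trial.

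A slip of the pen is also possible. The phrase used merges the names of the signed-rank and rank-sum tests, the sentence follows the rules for count data, and other wording in the section is garbled. A rank-sum comparison of graded response may have been meant. Against this, the same phrase is used earlier for paired data and Mann-Whitney is named separately. If it is a slip, the sentence still needs correcting.

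A statistical analysis plan that is not shown could supply what the article leaves out, but it does not make this sentence right.

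**Conclusion.** The sentence on the treatment effect is wrong as written. It names a within-group test for a contrast between independent groups, and the suitable tests in the same section are not linked to that contrast.

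That conclusion rests on the text and the design alone. The rates do not: about 73–75% at n = 30 and 92–93% at n = 50 depend on the assumed 2-point recovery, SD of 4 and arm size. With 1 to 3 points of recovery and 20 to 100 patients per arm, the rate runs from about 20% to 100%. With no recovery the problem disappears, because the test then holds its level. These figures illustrate the mechanism and do not predict this trial's error rate.

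**What to change.** Replace the sentence in section 2.8 with:

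> The treatment effect is evaluated by comparison between the thrombolysed and non-thrombolysed wake-up stroke groups, using the independent t test or Mann-Whitney U test for NIHSS (change from admission) and the chi-square or Fisher test for the mRS and responder outcomes. Within-group before/after tests are descriptive and are not used to judge efficacy.

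This uses only tests already in the section and outcomes already in section 2.6.2. It costs one sentence and no new data. Naming the two groups matters because section 2.4.2 produces three. Adjustment for admission NIHSS is an optional addition, provided that the scoring of deaths is specified; section 2.6.2 places death only within the worse response category.

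The change corrects the test only. Section 2.5.2 allocates thrombolysis in the wake-up stroke group by the DWI-FLAIR result, whereas sections 2.1 and 2.7 describe randomization. Those sections must be reconciled separately, since a between-group test compares treatments fairly only if the groups were formed by randomization.

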#### Grouping method

2.4.2

We will be divided into awakening stroke group (wake group whose morbidity is not exact) and ischemic stroke group (the group clarifying the time of onset) according to whether the onset time of the patient is clear. The awakening group is divided into the awakening group with thrombolytic therapy and the awakening group without thrombolysis according to whether they receive thrombolytic therapy.

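### One P < .05 rule covers about six unranked efficacy readouts, and the two groups to be compared are not identified although three are formed

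*Protocol article*

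**What the plan says.** **Decision rule.** Section 2.8 ends with one rule for all tests: two-sided, with P < .05 "indicating that the difference will be statistically significant". It does not distinguish between outcomes or comparisons.

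**Outcomes.** Section 2.6.2 has the NIHSS assessed "at the time of patient admission, 24 hours after treatment, and 7 days after treatment". It adds two categories based on a 4-point NIHSS change after 7 days: early effective, and invalid or worse (the latter also counts death). For the mRS it states: "We defined mRS score 0 to 1 points as cured and 0 to 2 points as good prognosis". None of these is called primary, and the text places the mRS only after discharge.

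**Groups.** Section 2.1 states: "This study will be a single-blinded, randomized controlled trial with 2 parallel groups". Section 2.4.2 first splits patients by whether onset time is known: "We will be divided into awakening stroke group (wake group whose morbidity is not exact) and ischemic stroke group". It then splits again: "The awakening group is divided into the awakening group with thrombolytic therapy and the awakening group without thrombolysis". Section 2.5.2 gives each of the three resulting groups its own treatment path.

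**Tests.** Section 2.8 provides two-group methods only: "the data of the same period between the 2 groups are compared using the independent *t* test method". It does not say which two groups. For the treatment effect it names the Wilcoxon signed rank test, which the same section uses for before-and-after data within one group.

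**The concern.** The Introduction gives the aim as the efficacy of intravenous thrombolysis in wake-up stroke. Of the three possible pairs, only wake-up thrombolysed versus wake-up not thrombolysed bears directly on that aim. Known-onset patients are all thrombolysed, so comparing them with thrombolysed wake-up patients says nothing about thrombolysis versus none. Comparing them with the non-thrombolysed wake-up group mixes treatment with type of stroke.

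Because neither the pair nor the outcome is fixed, whichever result falls below .05 can be put forward as the finding. The actual error rate of an efficacy claim is then above the 5% that the rule suggests. The within-group signed rank test adds another route: patients who recover spontaneously after stroke can give a small P value in that test without any drug effect.

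**Working it through.** **Inputs from the article**
- Level: two-sided .05 for each test (2.8).
- Efficacy readouts (2.6.2), six in all: NIHSS at 24 hours, NIHSS at 7 days, early effective, invalid or worse, mRS 0 to 1, mRS 0 to 2.
- Groups formed (2.4.2, 2.5.2): three, hence three possible pairs.

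**Inputs assumed**
- The correlation between readouts is not given. It is varied from 0 to 0.9, the same for every pair of readouts.
- Equal group sizes and normal test statistics.
- No true difference, and groups comparable apart from treatment.

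**The plan's own figure.** One outcome in one comparison gives 1 − 0.95 = 0.05, which is the stated level. The article states no family-wise rate to reproduce.

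**Independent tests**
- Six readouts, one pair: 1 − 0.95^6 = 0.265.
- Same, favourable direction only: 1 − 0.975^6 = 0.141, against 0.025 for one test.
- Eighteen tests (6 × 3), all treated as independent: 1 − 0.95^18 = 0.603. This cannot be attained, because the three pairs share groups.

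**Correlated tests.** Simulation under the global null, with six equicorrelated normal outcomes in three groups and the shared-group dependence kept. The table gives the chance of at least one P < .05.

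| Outcome correlation | Wake-up contrast, either direction | Wake-up contrast, favourable direction | All three pairs, either direction |
|---|---|---|---|
| 0 | 26% | 14% | 54% |
| 0.3 | 24% | 12% | 50% |
| 0.5 | 21% | 10% | 44% |
| 0.7 | 16% | 8% | 35% |
| 0.9 | 11% | 5% | 24% |

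**Where in the range the trial would lie.** The readouts overlap by construction. mRS 0 to 1 is contained in mRS 0 to 2, and the two early-response categories are built mainly from the 7-day NIHSS change. High correlations are therefore more plausible than low ones. Even at 0.9, the rate for the wake-up contrast is about twice nominal (11% against 5%, or 5% against 2.5% in the favourable direction).

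**After the change.** One primary outcome on one contrast returns the rate to 5%. Holm across six outcomes starts at .05 / 6 = .0083 for the smallest P value and keeps the family-wise rate at or below 5%.

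**The case against.** **The closing sentence of 2.8 is an ordinary statement of level and sidedness, and multiplicity is commonly left to an analysis plan.** This stands in part. The absence of an adjustment is not a finding here. An unseen plan would not, however, remove the conflict between two groups in 2.1 and three in 2.4.2, nor the unidentified pair in 2.8. The figures for study flow and assessment schedule are not shown and may settle which groups are compared and when the mRS is taken. The text should still agree with them.

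**A reader might infer that all three pairs will be tested on all six readouts as confirmatory tests, so that a false claim of efficacy is likely.** The article does not support this. It nowhere says that every pair is tested and never calls the tests confirmatory. Its aim is worded as observing efficacy, and the Discussion leaves effectiveness and safety to larger studies. The 60% figure needs an independence that shared groups rule out. A chance above one half needs all eighteen tests and nearly uncorrelated outcomes. Counting only results in favour of thrombolysis on the relevant contrast, the range is 5% to 14%.

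**The more serious problem is allocation.** This stands. Section 2.5.2 assigns wake-up patients to thrombolysis or general treatment by DWI-FLAIR result, whereas 2.1 declares randomization and 2.7 describes sealed envelopes. If allocation follows the MRI result, the two wake-up groups differ before treatment. The error rates above, which assume comparable groups, would then understate the problem.

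**Conclusion.** The point holds in limited form. The article fixes one blanket significance rule over about six unranked, overlapping readouts and does not identify the pair being compared, while contradicting itself on the number of groups. On the one contrast that addresses the aim, the chance of at least one false positive is about 11% to 26% (about 5% to 14% in the favourable direction, against 2.5%). Across all three pairs it would be about 24% to 54%, conditional on an analysis that the article does not state.

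These ranges rest on assumed correlations, a count of six readouts and comparable groups. They show a moderate inflation that is worth correcting, not that a false positive is probable. Correcting it would not by itself make the wake-up contrast a valid test of efficacy. That depends on how patients are allocated.

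**What to change.** In 2.1, 2.4.2 and 2.8:

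1. Reconcile the number of groups.
2. Name wake-up thrombolysed versus wake-up not thrombolysed as the single efficacy contrast, and treat the known-onset group as a descriptive reference without significance claims.
3. Test the treatment effect between those two groups, not with the within-group signed rank test.
4. Replace the blanket rule in one of two ways. Either name one listed outcome, at a stated time, as primary at two-sided .05 and report the others as secondary with confidence intervals, or apply Holm across the six readouts of that contrast.
5. Reconcile assignment by MRI result (2.5.2) with randomization and envelopes (2.1, 2.7). If allocation is by MRI result, say that the contrast cannot be claimed as randomized evidence of efficacy.

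Items 1 to 4 cost a few sentences and no additional patients or data. The price is that a lone P just under .05 on a secondary outcome or another pair no longer counts as proof. Item 5 is a question of design that the investigators must answer, and its cost depends on the answer.

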### Data management

2.9

The information obtained from each participant's evaluation will be recorded and printed on paper. Then, this information will be handwritten on the paper document case report form, which is used in the EXCEL file for future statistical analysis. According to the Personal Information Protection Act, we will not disclose the names of all participants and the unique identification numbers provided during this period to determine the participants. All participants will be informed that the clinical data obtained during the trial will be stored in the computer. Participants’ written consent will be stored by the lead investigator (Fig. 2).

**Figure 2 F2:**
[figure not shown]
Study design flow chart.

## Discussion

3

Intravenous thrombolytic therapy for ischemic stroke in the ultra-early stage has been proved to be an effective treatment in most randomized trials. However, ultra-early intravenous thrombolysis has a strict treatment time window (onset time <4.5 hours). Exceeding this treatment time window will increase the incidence of symptomatic intracranial hemorrhage, and severe cases may be life-threatening. WUS starts in sleep and is a more common form of ischemic stroke. Its incidence rate can be as high as 25%.^[17]^ Since patients or witnesses cannot provide accurate time of onset, the start time of stroke is still “normal at last.” Therefore, even if the patient or eyewitness finds out, the prescribed time window has already been exceeded. However, some recent research results prove that the original method does not seem appropriate. The study by Kim et al^[18]^ also focused on patients with WUS and stroke patients with unknown onset times during the day without witnesses. He found that nearly half of WUS patients will be immediately awake as soon as clinical symptoms appeared. Roveri et al^[19]^ divided the study subjects into 2 groups, the WUS group and the intravenous thrombolysis group within 3 hours of onset. Early CT manifestations will be applied to the early CT score of the Alberta Stroke Project (ASPECTS), and it was found that regardless of the risk factors and stroke severity Or the ASPECTS score is very close between the 2 groups. There was no statistically significant difference in the early CT scan ASPECTS scores between the 2 groups, indicating that the ischemic event of WUS patients occurred shortly before awakening or awakened as soon as the disease occurred. The author also pointed out that the prognosis of patients in the intravenous thrombolysis group was significantly better than that in the WUS group. The most representative epidemiological evaluation of WUS comes from a 2-center study of 1853 patients with ischemic stroke, including 273 WUS patients. The results show that compared with non-WUS patients, the incidence of WUS patients older age and higher NIHSS score on admission. However, if the time window is not considered, 35% of the patients are suitable for thrombolytic therapy. Then, if we can more accurately assess the onset time of WUS patients, a large number of patients will benefit from thrombolytic therapy. The study found that the mismatch of DWI/FLAIR has a high specificity and sensitivity for the judgment of patients within 3 to 4.5 hours. Thomalla et al^[20]^ observed 543 patients within 4.5 hours of onset. Under the field strength of 1.5 T, the specificity of DWI/FLAIR mismatch judgment of stroke patients within 4.5 hours of onset was as high as 78%. Morelli et al^[21]^ collected 27 WUS patients and 143 non-WUS patients and received intravenous thrombolysis. The results showed that the proportion of patients with mRS ≤1 point was 36.4%. The author mentioned in the conclusion that the selected WUS patients are suitable for intravenous thrombolysis. This study is based on the previous study, and has a purposeful choice for WUS patients who are given thrombolytic therapy. The imaging findings are consistent with DWI/FLAIR mismatch. In summary, we speculate that the selected WUS patients are safer to use intravenous thrombolytic therapy, which is expected to improve the patients’ early efficacy and long-term prognosis. However, whether the statistically significant benefits can be obtained remains to be observed by expanding the sample size. There is no consistent conclusion about the pathogenesis of WUS. WUS is more likely to manifest as small vessel disease. Male patients with sleep apnea are more likely to have WUS, and frequent snoring may be one of the mechanisms of WUS pathogenesis.^[22,23]^ The incidence of WUS patients is relatively high, and the effectiveness and safety of intravenous thrombolysis under the guidance of multimodality imaging treatment of WUS need to be further explored by prospective, large-scale studies.
